### Secondary outcomes

–First SBT pass rate–Need for post-extubation respiratory support (high-flow nasal cannula or noninvasive ventilation)–Length of pediatric ICU stay

### Sample size and power calculation

Based on a previous study by Ferguson et al.,^(15)^ we estimate that 94 patients per group (188 total) will be needed to detect non-inferiority with 90% power and a 10% non-inferiority margin. Considering a 20% attrition rate, we plan to recruit 170 participants.

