**Methods:**

This is a multicenter, open-label, non-inferiority randomized controlled trial. The primary outcome is successful liberation from invasive mechanical ventilation for at least 48 hours post-extubation. Secondary outcomes include the need for post-extubation respiratory support and the length of stay in the pediatric intensive care unit. The sample size is estimated to be 170 participants. Non-inferiority will be assessed using the Farrington-Manning test. The trial registration number is NCT06593288 (clinicaltrials.gov). Infants older than 36 weeks corrected gestational age and < 18 years old admitted to the pediatric intensive care unit requiring invasive mechanical ventilation for at least 24 hours and ready to wean will be included. Patients with chronic pulmonary conditions, congenital heart disease, upper airway abnormalities, morbid obesity, and in palliative care will be excluded. Patients who have passed the extubation readiness test will be randomized to receive either continuous positive airway pressure or pressure support during a spontaneous breathing trial.

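### The plan requires 188 patients for 90% power, allows for 20% attrition, and then recruits 170, so on its own figures it does not deliver 90% power

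*Protocol article*

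**What the plan says.** The Protocol article, section Sample size and power calculation, has two sentences on trial size. The first bases the calculation on a previous study and concludes that "94 patients per group (188 total) will be needed to detect non-inferiority with 90% power and a 10% non-inferiority margin". The second is "Considering a 20% attrition rate, we plan to recruit 170 participants".

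The abstract gives the same recruitment figure: "The sample size is estimated to be 170 participants". So 170 is the operative target and not a slip in one place.

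The section Statistical methods names the Farrington-Manning test with a 90% confidence interval, which corresponds to a one-sided 5% test. It also specifies an intention-to-treat primary analysis. The sample size section gives neither the assumed success rate nor the alpha.

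**The concern.** An allowance for attrition moves the recruitment target up from the number of evaluable patients needed. Here it moves down, from 188 to 170. The three statements (188 needed, 20% lost, 170 recruited) cannot all describe a trial with 90% power.

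In a non-inferiority trial, a power shortfall means a higher chance of an inconclusive result when CPAP truly is non-inferior. Ethics committees, funders and readers judge adequacy by this paragraph. They would be told that the risk of such a failure is 10%, when the recruitment plan implies a larger one.

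**Working it through.** **Inputs from the Protocol article**
- Requirement: 94 per group, 188 in total, at 90% power.
- Margin: 10%, read as 10 percentage points on the difference in success.
- Attrition: 20%. Recruitment: 170, which is 85 per group at the equal allocation implied by the group sizes.
- Alpha: not given for the calculation. One-sided 5% follows from the 90% confidence interval; one-sided 2.5% was tried as well.
- Success rate: not given, so it is back-solved below as an assumption.

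**Step 1: the attrition step**
- Correct inflation: 188/(1 − 0.20) = 235 (94/0.80 = 117.5, so 118 per group and 236 for equal groups).
- Cruder inflation: 188 × 1.20 = 225.6, so 226.
- Neither gives 170.
- Without loss, 170 is 188 − 170 = 18 short.
- With 20% loss, 170 × 0.80 = 136, or 68 per group. That is 188 − 136 = 52 short, and 1 − 68/94 = 28% below requirement.

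This step needs no outside figure.

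**Step 2: reproduce 94 per group**

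With equal true success p in both arms and unpooled variance:

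n per group = (z_α + z_β)² × 2p(1 − p) / 0.10²

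At one-sided 5% and 90% power, (1.645 + 1.282)² = 8.564. Setting n = 94 gives p = 0.942: 8.564 × 2 × 0.9417 × 0.0583 / 0.01 = 94.0. At one-sided 2.5% the same solution is p = 0.953. So 94 per group is attainable, but the text does not show which inputs were used.

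**Step 3: power at the planned size**

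Under this formula, if 94 per group gives 90%, then power at n per group is

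Φ[(z_α + 1.282) × √(n/94) − z_α]

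At one-sided 5%:
- n = 85: Φ(2.926 × 0.951 − 1.645) = Φ(1.138) = 87.2%
- n = 68: Φ(2.926 × 0.851 − 1.645) = Φ(0.844) = 80.1%

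The same two sizes under other calibrations to 94 per group:

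| Calibration | Implied success | 85 per group | 68 per group |
|---|---|---|---|
| Unpooled, one-sided 5% | 94.2% | 87.2% | 80.1% |
| Unpooled, one-sided 2.5% | 95.3% | 86.9% | 78.7% |
| Farrington-Manning approximation, one-sided 5% | 95.7% | 87.1% | 78.5% |
| Farrington-Manning approximation, one-sided 2.5% | 97.2% | 86.3% | 75.0% |
| Farrington-Manning, exact enumeration, one-sided 5% | 95.7% | 88% | 83% |

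In the last row, exact power at 94 per group is 91%.

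**Step 4: the named test at the 94.2% rate**

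If the sample size did come from the unpooled formula with 94.2% success, exact Farrington-Manning power at one-sided 5% is 85.5% at 94 per group, 81.3% at 85 and 75.0% at 68. At 90% success it is 72%, 67% and 60%. These figures combine two effects, the change of test or success rate and the smaller sample. Only the fall from 94 to 85 or 68 belongs to the present point.

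**Step 5: a possible origin of 170**

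At one-sided 5% and p = 0.942, 80% power needs (1.645 + 0.842)² × 2 × 0.9417 × 0.0583 / 0.01 = 67.9, so 68 per group, and 2 × 68/0.80 = 170 exactly. This suggests that an 80%-power recruitment target was attached to a 90%-power statement. It is an inference: at one-sided 2.5%, 80% power needs 70.2 per group, about 176 after inflation, and the match disappears.

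**The case against.** The strongest reply is that the document does not show which figure is wrong. If 94 per group is the misprint, 90% power could still hold at 170: with 97.2% success in both arms and one-sided 5%, exact Farrington-Manning power at 68 per group is 90.2%. That is arithmetically correct, but it requires discarding the plan's stated requirement and supplying a success rate that the plan does not give. The paragraph would need correcting in that case too.

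A second reply is that attrition should be small, because the outcome is reintubation within 48 hours and the analysis is by intention to treat. This has some force. With no loss, the risk of failing to show non-inferiority is about 13% and not about 20%; the doubling of the stated 10% applies only if the full 20% is lost. But the 20% is the plan's own assumption. Randomisation also precedes the breathing trial while the outcome is counted from extubation, so some randomised patients may not reach the outcome window. Even with no loss, 85 per group is below 94.

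Third, the size of the shortfall depends on the calibration. Calibrated to the Farrington-Manning test itself by exact enumeration, the loss from 94 per group is about 3 to 8 points. This bounds the magnitude but does not remove the contradiction. The lower figures in Step 4 should not be attributed to this error alone.

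That this is a condensed article is no answer: two incompatible figures stand in consecutive sentences, and no longer document could make both right.

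**Conclusion.** The concern holds. Taking the stated requirement of 188 for 90% power as given, 170 recruits do not deliver that power, with or without attrition. This rests only on figures in the document.

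The size of the shortfall rests on a back-solved success rate and an alpha inferred from the confidence interval. Across the calibrations that honour 94 per group, power is about 86% to 88% if all 170 are analysed and about 75% to 83% after 20% attrition. The central values at one-sided 5% with the unpooled formula are 87% and 80%. None of them reaches 90%. The suggestion that 170 came from an 80%-power calculation is plausible but unproven, and the conclusion does not depend on it. This must be corrected, because the headline size and the headline power cannot both stand.

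**What to change.** Revise the Sample size and power calculation section, and the abstract if the target changes, so that evaluable number, attrition, recruitment target and power agree. State the assumed success rate in each arm and the one-sided alpha, and compute power for the Farrington-Manning test that will be used. There are two consistent routes:

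- **Keep 170.** Replace the 90% claim with the power that 170 delivers, both with all patients analysed and with 136 evaluable. On the unpooled one-sided 5% calibration these are about 87% and 80%. They are placeholders until the sponsor's own inputs are put through the Farrington-Manning calculation, which may give different values.
- **Keep 90% power with 94 per group.** Set recruitment at 235, or 236 for equal groups.

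If 94 per group is itself the error, give the corrected requirement with its inputs.

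The first route costs a text correction and a less favourable power statement, and needs no extra patients. The second adds 235 − 170 = 65 patients (66 for equal groups) to a two-centre trial planned to recruit for about a year. Under either route, check the registry entry, which was not available for this review, and align it if it carries the same figures.

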### Statistical methods

The primary analysis will be performed according to the intention-to-treat principle. Non-inferiority will be assessed using the Farrington-Manning test, with a 90% confidence interval to confirm the non-inferiority of CPAP compared to PS.

### Data collection and management

Data will be collected on patient demographics, clinical details, and ventilator settings, and stored in a secure online database (REDCap).

### Harms and adverse events

Adverse events will be documented, and serious adverse events will be reported to the ethics committee within 24 hours.

### Patient and public involvement

The research was developed to improve ventilation liberation in pediatric ICU settings, though patients were not involved in the design or recruitment process. Results will be disseminated through peer-reviewed publications.

## DISCUSSION

We present the design and rationale of the "Non-inferiority randomized controlled trial of SBT in children with and without pressure support", which aims to determine whether CPAP alone during an SBT is non-inferior to CPAP combined with PS in predicting successful extubation in mechanically ventilated children. The trial is designed as a multicenter, randomized, non-inferiority study, with the primary outcome being successful liberation from MV for at least 48 hours post-extubation. Secondary outcomes include the need for additional respiratory support post-extubation and the length of pediatric ICU stay. Protocol publication increases research transparency, facilitates future publication of results, avoids research duplication, and informs the community.

There is a scarcity of clinical trials in patients under MV, particularly on the best practices related to weaning and liberation from MV. This study will provide valuable data to guide clinical decision-making and influence future guidelines on weaning from MV in pediatric critical care.

A limitation of this trial is that the unblinded design may introduce bias. The 1-hour SBT duration is based on current practice, but this study may not address the optimal duration.

## Data Availability

The contents will be made available at the time of publication of the article.
